### Interventions

First, all the patients will undergo laparoscopic surgery. Patients require gastroscopy biopsy pathology results to confirm the diagnosis, and endoscopic ultrasound and abdominal enhanced CT to evaluate the clinical stage and tumor location before surgery. To assess the general state of the patient and the risk of surgery, patients also need laboratory examinations including routine blood tests, blood biochemical tests, coagulation function tests, lung function tests, echocardiogram, and chest CT.

All patients will undergo supine and split leg surgery. We will use the following methods for puncture port placement: (a) Insert a 12 mm trocar through a 1 cm transverse incision under the navel to establish a pneumoperitoneum and maintain the pressure at 12–15 mmHg. This opening will also be used for observation. (b) Insert a 12 mm trocar 2 cm below the costal margin of the left anterior axillary line as the surgeon's main operation opening. (c) Insert a 5 mm trocar 1 cm above the navel of the left mid-clavicular line as an auxiliary operating opening for the surgeon. (d) Insert a 5 mm trocar 2 cm below the costal margin of the right anterior axillary line as a secondary operation opening for the assistant. (e) Insert a 12 mm trocar 1 cm below the midpoint of the connection between opening A and opening D as the assistant's main operation opening. The location of the puncture opening is shown in Figure 2.

**Figure 2 F2:**
[figure not shown]
Puncture port placement.

### Experimental group

We take the 4sb LNs at the first branch of the LGA and take the 12a LNs in the anterior area of the PHA. LNs in the two areas will be pathologically tested separately. The two groups of LNs will be separated and removed by the surgeon during the operation, rather than trimmed from the whole *ex vivo* pathological specimen.

The scope of 4sb LND is as follows: we choose to cut off the LGA at the beginning of the first branch of the LGA, and then sweep along the greater curvature to the LGA and the right gastroepiploic artery interchange (Figure 3).

**Figure 3 F3:**
[figure not shown]
Schematic diagram of the scope of 4sb lymph node dissection. The yellow area is the experimental group, and the yellow plus purple area is the control group.

The scope of 12a LND is as follows: (I) Upper border: the confluence of the right and left hepatic artery. (II) Lower border: the upper border of the pancreas at the origin of the PHA. (III) Right border: the left side of the bile duct. (IV) Left border: the left border of ligamentum hepatoduodenal. (V) Anterior border: the anterior hepatoduodenal ligament. (VI) Posterior border: the anterior side of the PHA (Figure 4).

**Figure 4 F4:**
[figure not shown]
Schematic diagram of the scope of 12a lymph node dissection. The yellow area is the experimental group, and the yellow plus purple area is the control group.

### Control group

We take the 4sb LNs at the first branch and the root of the LGA and take 12a LNs in the anterior and posterior areas of the PHA. LNs in the two areas will be pathologically tested separately. The two groups of LNs will be separated and removed by the surgeon during the operation, rather than trimmed from the whole *ex vivo* pathological specimen.

The scope of 4sb LND is as follows: we choose to cut off the LGA at the root of the LGA originating from the splenic artery, and then sweep along the greater curvature to the LGA and the right gastroepiploic artery interchange (Figure 3).

The scope of 12a LND is as follows: posterior border is the anterior side of the portal vein. The remaining borders are the same as the experimental group (Figure 4).

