The advantage of the traditional lymphadenectomy is that it thoroughly cleans the regional lymph nodes (LNs). However, there are important blood vessels around the 4sb and 12a LNs, such as the splenic artery and portal vein. The risk of vascular damage is higher, the operation is difficult, and the operation time is long. Patients with advanced lower third gastric cancer have a low rate of 4sb and 12a LNM, and the prognosis is poor. Therefore, we designed a new cleaning range. We divided the 4sb LNs into two parts, namely those at the root of the LGA and the peripheral LNs of the first branch. 12a LNs were divided into two parts, namely the anterior and posterior peripheral LNs of the PHA. According to the patient's condition, we will take the 4sb LND area as the first branch LNs of the LGA, saving those at the root, and take the 12a LNs in the anterior area of the PHA, saving those in the posterior area, in some patients. The purpose is to simplify the operation, shorten the operation time, reduce the surgical complications, and speed up the recovery of the patient while obtaining the same radical cure effect. However, the efficacy and safety of this new technique is still unclear.

Since the scope of 4sb and 12a LND is not uniform nationally and internationally and there are few studies on the effectiveness and safety of different anatomical scopes, clinical study on the scope of 4sb and 12a LND is necessary. Therefore, we designed this experiment to compare the pathology, safety, efficacy, and prognosis of the new and traditional methods of 4sb and 12a lymphadenectomy to provide a new, alternative lymphadenectomy for patients with gastric cancer.

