### Primary outcome

The primary outcome is the 12a lymph node metastatic rate. The 12a lymph node metastatic rate is equal to the number of patients with 12a LNM divided by the total number of patients enrolled.

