### Secondary outcomes

The secondary outcome has four parts: pathology data, efficacy index, safety index, and follow-up data. The pathology data comprises the 4sb lymph node metastatic rate, the number of 4sb LNs dissected, the number of 12a LNs dissected, and tumor pathological staging. The efficacy evaluation index comprises operation time, intraoperative blood loss, and postoperative recovery status (time to get out of bed, time to pass gas, time to liquid food intake, time to semi-liquid food intake, and postoperative hospital stay). The safety evaluation index comprises complications and mortality ≤30 days after surgery. Intraoperative complications include injuries of the hepatic artery, common bile duct, portal vein, spleen and pancreas. Postoperative complications include biliary fistula, delayed hepatic artery and portal vein hemorrhage, pancreatic fistula, and other pancreatic injury-related complications. Follow-up data comprises 3-year or 5-year disease-free survival and OS.

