### Data collection

We will use numbers instead of the name and sex of the enrolled patient to protect the privacy of the patient. Electronic data capture (EDC) system will be used to collect clinical data. The following data will be collected: (I) demographic, including sex, age, body mass index and concomitant disease; (II) perioperative laboratory test results, including those of routine blood and biochemical tests; (III) auxiliary examination results, including those of gastroscopy biopsy, endoscopic ultrasound and abdominal enhanced CT; (IV) surgical data, including operation time, blood loss, surgical method, extent of lymphadenectomy and intraoperative complications; (V) postoperative recovery data including time to get out of bed, time to pass gas, time to liquid food intake, time to semi-liquid food intake, postoperative hospital stay; and (VI) postoperative pathology, including pathological stage, the number of 4sb and 12a LNs dissected and metastasis rate (Table 1).

**Table 1 T1:** Checklist for clinical data collection and follow-up plan of enrolled patients.

	Baseline		Post-operation					Follow-up							
	Before operation	Operation	POD1	POD3	POD5	POD7	POD30	3 m	6 m	12 m	18 m	24 m	36 m	48 m	60 m
Inclusion/Exclusion criteria	×														
Informed consent	×														
Demographic information	×														
Laboratory tests	×	×	×	×	×	×		×	×	×	×	×	×	×	×
Operation information		×													
Postoperative recovery status			×	×	×	×	×								
Physical examination	×							×	×	×	×	×	×	×	×
Chest CT	×									×		×	×	×	×
Abdomen enhanced CT	×							×	×	×	×	×	×	×	×
Gastroscopy	×									×		×	×	×	×
Ultrasound gastroscope	×														
Pathology	×					×									
Complications							×								
Mortality							×	×	×	×	×	×	×	×	×
Recurrence								×	×	×	×	×	×	×	×

*“×”, the need to collect the clinical data.*

*POD, postoperative day.*

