Huang (17) pointed out that the posterior boundary of 12a LND was defined as the anterior edge of the portal vein, so only the LNs in front of the portal vein were cleaned during the operation. Huang (14) published a new 12a LND sequence, suggesting that the portal vein should be exposed first and the LNs before the portal vein should be cleaned. However, we considered that the 12a lymph node metastatic rate is lower for advanced lower third gastric cancer, and LNM around the portal vein is even more rare. Therefore, we suggested that only the LNs area in the front of the PHA should be cleaned, retaining the LNs area around the portal vein. The same is true for the 4sb LNs. We suggested cleaning the LNs around the first branch of the LGA and retaining the LNs around the root of the LGA. Through such a cleaning method, under the premise of ensuring the radical cure of the tumor, the risk of damage to blood vessels and organs, and complications during surgery, are reduced.

Although ESMO, NCCN and JGCA regularly update the guidelines for treating gastric cancer, they are all updated in terms of indications of the extent of LND, and there is no further detailed update of the definition of LND (4–6). In addition, although there have been some studies on 4sb and 12a LNs, the majority are related to LNM and risk factors or survival rates. Therefore, we are currently conducting a clinical trial to establish a safer 4sb and 12a LND range, to reduce the complication rate of D2 lymphadenectomy while obtaining the same radical cure effect.

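### The primary outcome compares 12a metastatic rates over different tissue in the two groups, and no stated outcome uses the control group to estimate disease confined to the omitted nodes

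*Protocol article*

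**What the plan says.** The Introduction splits each station in two. For 12a, "12a LNs were divided into two parts, namely the anterior and posterior peripheral LNs of the PHA"; 4sb is split into root and first-branch nodes. The new technique is to "take the 12a LNs in the anterior area of the PHA, saving those in the posterior area, in some patients", and likewise to leave the 4sb root.

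Under Experimental group, the 12a field ends at "Posterior border: the anterior side of the PHA". Under Control group it extends back to the front of the portal vein, and the surgeons "take 12a LNs in the anterior and posterior areas of the PHA. LNs in the two areas will be pathologically tested separately". The sentence about testing two areas separately also stands, word for word, under Experimental group.

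The primary outcome makes no distinction by sub-area: "The 12a lymph node metastatic rate is equal to the number of patients with 12a LNM divided by the total number of patients enrolled". The secondary outcomes are also by station: "The pathology data comprises the 4sb lymph node metastatic rate, the number of 4sb LNs dissected, the number of 12a LNs dissected", plus tumour stage. So is the pathology item under Data collection: "postoperative pathology, including pathological stage, the number of 4sb and 12a LNs dissected and metastasis rate".

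The Discussion gives the premise of the technique: 12a metastasis is infrequent in these patients, and "LNM around the portal vein is even more rare".

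Under Study design, the surgeon assigns patients 1:1. Experimental patients whose 4sb and 12a nodes are found positive on imaging or at operation are moved to the control group.

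**The concern.** The experimental 12a field is a subset of the control field, so one outcome name covers two different measurements. A patient whose only 12a metastasis is posterior counts as positive in the control group and negative in the experimental group. A lower experimental rate could then reflect disease left behind, a different mix of patients, or both, and the comparison cannot tell these apart. Case mix matters here because the surgeon allocates and node-positive experimental patients are moved across.

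The premise that disease in the omitted area is rare can be checked by histology only in the control group, where that area is removed. No stated outcome does so, for 12a or for 4sb. If the control sub-areas are pooled before they reach pathology, the information is lost and cannot be recovered at analysis.

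**Working it through.** **1. Tissue examined, by group**

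| Sub-area | Experimental | Control |
|---|---|---|
| 4sb first branch | removed | removed |
| 4sb root | left | removed |
| 12a anterior | removed | removed |
| 12a posterior | left | removed |

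Only the first-branch 4sb and anterior 12a rates are measured over the same tissue in both groups.

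**2. The plan's own sample size**

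Inputs from Sample size: control rate 9.1%, margin −7.4 points, one-sided α 0.025, power 80%, loss 10%. With equal true rates and unpooled variance:

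n = (1.960 + 0.842)² × 2 × 0.091 × 0.909 / 0.074² = 237.1, so 238 per group. Then 238 × 1.10 = 261.8, so 262 per group and 524 in total. The stated figure reproduces.

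It reproduces with equal observed rates. With comparable groups, that means no posterior-only metastasis at all.

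**3. Precision of the planned comparison**

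Evaluable after 10% loss: 262 × 0.90 = 235.8, so 236 per group.

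95% half-width = 1.96 × √(2 × 0.091 × 0.909 / 236) = 0.0519, or 5.2 points.

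**4. Effect of posterior-only disease on the planned test**

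Assume comparable groups, and that d points of the 9.1% lie only posteriorly. The experimental rate is then 9.1% − d, and

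power = Φ[(0.074 − d)/SE − 1.96], with SE the unpooled standard error at 236 per group.

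| d (assumed) | Experimental rate | SE | Power |
|---|---|---|---|
| 0 | 9.1% | 0.0265 | 80% |
| 1 point | 8.1% | 0.0258 | 70% |
| 2 points | 7.1% | 0.0251 | 58% |

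The margin corresponds to a detected experimental rate of 9.1 − 7.4 = 1.7%. That is 7.4/9.1 = 81% of control-level positivity going unseen.

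**5. What the control group could show**

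Exact (Clopper–Pearson) upper limits of the 95% CI for the share of controls positive only in the omitted area. With 0 events the limit is 1 − 0.025^(1/n). The documents give no posterior-only or root-only rate, so the event counts are assumptions.

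| Controls analysed | 0 events | 3 events |
|---|---|---|
| 262 | 1.4% | 3.3% |
| 236 | 1.6% | 3.7% |
| 200 (assumed, after restricting to node-negative controls) | 1.8% | 4.3% |

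**6. Whether the sub-areas are kept apart**

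Under Experimental group only one 4sb area and one 12a area are taken, so two areas there can only mean 4sb and 12a. The identical sentence under Control group follows a list of four sub-areas. It can mean 4sb versus 12a again, or the two halves of each station. The text does not settle which.

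**The case against.** The strongest objection is that the control-group rate is not a clean answer either. A reader might infer that it answers the trial's question directly and does not depend on how patients were divided. The documents do not support that. The surgeon assigns patients, and the Introduction says the reduced scope is chosen according to the patient's condition, so the rate depends on who is placed in control. Excluding only the patients moved across would not be enough: the screen for visibly positive nodes applies to the experimental group alone, so controls who would not have received the reduced dissection would remain and probably push the rate up. This stands, and it is why the analysis set needs restricting.

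A reader might also take it as settled that the control sub-areas are tested separately. The repeated sentence does not establish this, and if they are not, the surgeon has an extra separation to make.

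Nor are the omitted nodes wholly unassessed. They get no histology, but imaging and intraoperative assessment are used, and recurrence and survival are followed. 4sb is not ignored: its station-level rate is a secondary outcome.

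The precision comparison is partly hypothetical. It sets a difference of two 9.1% rates against one proportion assumed near zero, so much of the gain comes from the assumed low rate and the change of quantity estimated. The power losses assume comparable groups and concern the sample-size assumption, which this remedy leaves alone.

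Finally, an article may leave sub-area tabulations to a fuller document. But it does define its primary and secondary outcomes, and defines them by station, so this is more than missing detail.

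**Conclusion.** The point holds in a limited form. The primary outcome compares whole-station 12a rates over different tissue, posterior-only disease is invisible to histology in the experimental group, and no stated outcome uses the control group's posterior 12a or 4sb-root result, although the technique rests on disease there being rare.

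The between-group difference is known to about ±5.2 points at 236 per group, taking both rates as 9.1%. A control-group rate for the omitted area would have an upper limit of 1.4% to 1.6% with no events and 3.3% to 3.7% with three, on assumed counts and 236 to 262 patients; restriction to node-negative controls widens these somewhat.

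That estimate avoids the cross-group comparison but not the surgeon's choice of who enters the control group. It does not replace the safety, recurrence and survival outcomes. A reader might conclude that it must be co-primary. Nothing in the document requires that, and a co-primary would need a success threshold and a rule for multiplicity. A key secondary outcome is sufficient.

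**What to change.** 1. State that control specimens are labelled and recorded as four sets: 4sb first branch, 4sb root, 12a anterior and 12a posterior. Replace the two-areas sentence under Experimental group and Control group with wording that says which sets are meant in each.
2. Add two key secondary outcomes: the proportion with metastasis only in the posterior part of 12a, and the proportion with metastasis only in the root part of 4sb, each with an exact 95% CI. The analysis set is patients originally assigned to control whose 4sb and 12a nodes were negative on imaging and at operation, the condition Study design applies to the experimental group. Report moved-in patients separately.
3. Compare the anterior 12a rate between groups, so that the same tissue is compared. State that this comparison still carries the allocation bias that the Conclusion concedes.

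The cost is extra labels, EDC fields and outcome text, plus recording the imaging and intraoperative node status of controls if this is not already captured. If the sub-areas are not yet kept apart in the operation, the surgeon must also separate them. The sample size and the extent of dissection do not change. The labelling needs settling while patients are still being enrolled, because pooled specimens cannot be divided afterwards.

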### Perioperative treatment

Patients will receive symptom-based treatment after surgery, including electrocardiogram monitoring, intravenous fluid replacement, acid suppression, and pain relief. Routine blood tests, biochemical tests, measurement of drainage fluid amylase, and drainage fluid characteristics will be regularly monitored to observe whether bleeding, biliary fistula, and pancreatic injury-related postoperative complications occur. The discharge standards are as follows: gastrointestinal function is restored, the patient can have a semi-liquid diet, and the abdominal drainage tubes are removed.

### Data collection

We will use numbers instead of the name and sex of the enrolled patient to protect the privacy of the patient. Electronic data capture (EDC) system will be used to collect clinical data. The following data will be collected: (I) demographic, including sex, age, body mass index and concomitant disease; (II) perioperative laboratory test results, including those of routine blood and biochemical tests; (III) auxiliary examination results, including those of gastroscopy biopsy, endoscopic ultrasound and abdominal enhanced CT; (IV) surgical data, including operation time, blood loss, surgical method, extent of lymphadenectomy and intraoperative complications; (V) postoperative recovery data including time to get out of bed, time to pass gas, time to liquid food intake, time to semi-liquid food intake, postoperative hospital stay; and (VI) postoperative pathology, including pathological stage, the number of 4sb and 12a LNs dissected and metastasis rate (Table 1).

**Table 1 T1:** Checklist for clinical data collection and follow-up plan of enrolled patients.

	Baseline		Post-operation					Follow-up							
	Before operation	Operation	POD1	POD3	POD5	POD7	POD30	3 m	6 m	12 m	18 m	24 m	36 m	48 m	60 m
Inclusion/Exclusion criteria	×														
Informed consent	×														
Demographic information	×														
Laboratory tests	×	×	×	×	×	×		×	×	×	×	×	×	×	×
Operation information		×													
Postoperative recovery status			×	×	×	×	×								
Physical examination	×							×	×	×	×	×	×	×	×
Chest CT	×									×		×	×	×	×
Abdomen enhanced CT	×							×	×	×	×	×	×	×	×
Gastroscopy	×									×		×	×	×	×
Ultrasound gastroscope	×														
Pathology	×					×									
Complications							×								
Mortality							×	×	×	×	×	×	×	×	×
Recurrence								×	×	×	×	×	×	×	×

*“×”, the need to collect the clinical data.*

*POD, postoperative day.*

### Follow-up

We will arrange for a full-time nurse to be responsible for enrolled patients postoperative follow-up in the hospital, and the outpatient clinic after discharge. The follow-up time points are 3, 6, 12, 18, 24, 36, 48, and 60 months. During the follow-up period, the patients need to receive physical and laboratory examinations, chest CT, abdominal enhanced CT, and gastroscopy. Laboratory examinations will include routine blood and biochemical tests (Table 1).

### Adverse events

A serious adverse event (SAE) refers to any adverse medical event, whether related to surgery or not. All SAEs will be recorded and reported to the ethics committee of Beijing Friendship Hospital within 24 h for enrolled patients. During the research period, the data monitoring committee will follow the standard procedures of clinical trials and supervise safety data in an unblinded manner.

Patients that have postoperative complications will receive the best therapy. Meanwhile, the enrollment will be suspended if the incidence of SAE exceeds 5% of enrolled patients. The Efficacy and Safety Evaluation Committee (ESEC) will evaluate whether to continue this study.

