### Sample size

The sample size was calculated using PASS 11.0 software. The 12a lymph node metastatic rate was used as the main result in the sample size calculation. This study assumes that the 12a lymph node metastatic rate in the experimental group is not inferior to the control group. According to published literature (9), the 12a lymph node metastatic rate of the control group is estimated at 9.1%. Combined with clinical practice, the non-inferiority threshold is set to −7.4%. The size of the two groups of patients was determined with a 1:1 design, setting a significance level of *α* = 0.025 (unilateral), power at 80%, and loss to follow-up at 10%. We expect 524 patients to be registered, with 262 patients in each group.

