### Interim analyses

When the number of enrolled patients reaches 262, we will perform statistical analysis on the primary and secondary outcomes. The independent statistical team will be responsible for the interim analysis and report the results to the DSMC. The DSMC will discuss the results and report to the ESEC. If the effectiveness and safety of the experimental group are significantly lower than that of the control group, the study will be suspended.

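### The SAE definition has no seriousness condition, so the 5% suspension rule built on it would, read literally, be set off early by ordinary postoperative events

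*Protocol article*

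**What the plan says.** Three statements in the protocol article's Adverse events section belong together.

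- Definition: an SAE "refers to any adverse medical event, whether related to surgery or not".
- Trigger: "the enrollment will be suspended if the incidence of SAE exceeds 5% of enrolled patients".
- Consequence: "The Efficacy and Safety Evaluation Committee (ESEC) will evaluate whether to continue this study".

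The same section sends every SAE to the ethics committee within 24 hours and has the data monitoring committee "supervise safety data in an unblinded manner". The trigger's denominator is all enrolled patients, both groups together. The article does not say whether events or patients are counted, over what period, or how often the proportion is checked.

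Groups are compared elsewhere. Under Interim analyses: "When the number of enrolled patients reaches 262, we will perform statistical analysis on the primary and secondary outcomes", and "If the effectiveness and safety of the experimental group are significantly lower than that of the control group, the study will be suspended". Under Monitoring and quality assurance, the DSMC has unrestricted access to the data and may carry out emergency review of safety issues.

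**The concern.** The sentence headed as a definition of a serious adverse event in fact defines an adverse event of any grade and any cause. Taken alone that would be a drafting slip. Here a suspension rule and a 24-hour reporting duty both hang on it. If staff follow the text, minor and unrelated events after gastrectomy count towards a 5% limit and recruitment stops for reasons that say little about the dissection under study. If staff apply an unwritten standard of seriousness instead, the rule in force is not the rule on paper, and nobody can say afterwards whether the limit was reached.

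The limit is also pooled. Reaching it tells the reviewing committee that events have occurred, but not in which group, although comparing the safety of the two dissections is one of the study's stated purposes.

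**Working it through.** **Inputs from the article.** Limit: more than 5% of enrolled patients, pooled. Planned size: "We expect 524 patients to be registered, with 262 patients in each group". Interim look: 262 enrolled. The 5% limit comes without a derivation, so there is no figure of the plan's own to reproduce.

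**Assumptions, not in the article.**
- The proportion p of patients with at least one event, taken as 3%, 5%, 10% and 20%.
- The checking schedule: after every patient, or at a single look.
- Each patient counts at most once, patients are independent, and a patient's event is known when that patient enters the denominator. In practice events arrive somewhat later, which would move the earliest triggers back.

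**Step 1: the smallest count that exceeds the limit.**
- 1/19 = 5.3% exceeds it; 1/20 = 5.0% does not. A single affected patient among the first 19 is enough.
- At 50 enrolled: 2/50 = 4.0%, 3/50 = 6.0%, so 3 patients.
- At 262 enrolled: 13/262 = 4.96%, 14/262 = 5.3%, so 14 patients.

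**Step 2: checking after every patient.** While n ≤ 19 the rule is set off by the first event, so P(triggered by patient n) = 1 − (1 − p)^n.
- p = 10%: 1 − 0.9^6 = 0.47 and 1 − 0.9^7 = 0.52, so the median is patient 7. By patient 19: 1 − 0.9^19 = 0.86.
- p = 20%: 1 − 0.8^3 = 0.49 and 1 − 0.8^4 = 0.59, so the median is patient 4. By patient 19: 1 − 0.8^19 = 0.99.

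The probability of at least one trigger by patient 524 follows from carrying the cumulative binomial count forward and removing each path at its first crossing.

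**Step 3: a single look.** At 50 patients, P(X ≥ 3) with X ~ Bin(50, p). For p = 10%: 1 − (0.9^50 + 50·0.1·0.9^49 + 1225·0.1²·0.9^48) = 1 − (0.0052 + 0.0286 + 0.0779) = 0.888. At 262 patients, P(X ≥ 14) with X ~ Bin(262, p).

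| p (assumed) | Every patient, by 524 | Median patient | One look at 50 | One look at 262 |
|---|---|---|---|---|
| 3% | 59% | 38 | 19% | 3% |
| 5% | 92% | 14 | 46% | 44% |
| 10% | certain to rounding | 7 | 89% | 99.8% |
| 20% | certain to rounding | 4 | 99.9% | certain to rounding |

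At 3%, repeated checking that starts only at patient 100 gives 22%.

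**Step 4: what the trigger says about the groups.** Take 262 enrolled, 131 per group, and 14 affected patients. A split of 7 against 7 (Fisher p = 1.0) and a split of 14 against 0 (Fisher p < 0.001) reach the limit in exactly the same way.

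**The case against.** The article condenses a fuller protocol, so a checking schedule, a minimum number enrolled or a formal boundary may be set out there. That stands: their absence is not the finding. The definition, however, is stated and not omitted, and added detail elsewhere could not turn any adverse event into a serious one without contradicting it.

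Early suspension rests on assumptions. That also stands. At 3% with one look at 262 patients, the rule would be set off only about 3% of the time. But rates near 3% suit events that are truly serious. The defect is that all events count, which implies higher rates, and at 10% or more the rule is set off early under nearly any schedule.

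Three stronger readings are tempting, and the documents do not support them.

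- *A pooled limit would hide a real excess in one group.* Rates of 8% and 2% average exactly 5%, so a reader might infer that the limit is not exceeded. That ignores chance variation. With patients alternating between those rates, the rule is set off with probability about 92% if checked after every patient and about 87% if checked from patient 50. The pooled trigger is uninformative about the source; it is not silent.
- *Nothing in the plan compares safety between groups.* Unblinded supervision, DSMC emergency review and the interim analysis at 262 all do so, and the secondary outcomes at that interim include complications and deaths within 30 days. None of these is tied to the 5% rule, but they exist.
- *The study would be ended.* The rule suspends enrolment and passes the decision to the ESEC. It changes no estimate or test.

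**Conclusion.** The point holds as an error in stated text: the SAE definition and the 5% rule do not work together. Followed as written, and if at least 10% of patients have some adverse event, enrolment is suspended early. That rate is an assumption, though a low one for events of any kind after D2 gastrectomy. At lower rates the outcome depends heavily on how often the proportion is checked, and the article does not say. The 59% at a 3% rate reflects repeated checking of a small denominator and would persist after the definition is corrected, so it should not be read as the effect of the wording alone. The pooled trigger cannot identify the group responsible, which limits its use to the committee but does not leave the trial without between-group safety review. The consequence is operational: avoidable suspensions, over-reporting within 24 hours, and doubt about which rule is in force.

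**What to change.** Reconcile the two statements in the Adverse events section:

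1. Add a seriousness condition to the SAE definition and keep non-serious events as adverse events, recorded separately.
2. Express the limit as patients with at least one SAE over patients enrolled, and state the period over which events count, if the full protocol does not already do so.
3. When the limit is reached, have the data monitoring committee review the counts by group before the ESEC decides on continuation.

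A minimum number enrolled, a by-group limit or a calculated boundary would be reasonable refinements for the monitoring charter, but they are preferences and not needed to remove the error. The numerical limit remains a matter for the sponsor and the committee. The cost is a short wording amendment; the committees and the unblinded safety supervision are already in place.
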